## Abstract

**Background:**

Although clinical guidelines prioritize the treatment of depression and anxiety in young persons, there is accumulating evidence that the presence of symptoms of borderline personality disorder (BPD) is associated with the limited effectiveness of these standard treatments. These findings stress the need for interventions addressing early-stage BPD in young people with presenting symptoms of anxiety and depressive disorders. The aim of this study is to investigate the (cost-)effectiveness of an early intervention programme for BPD (MBT-early) compared to first-choice psychological treatment for depression and anxiety according to Dutch treatment guidelines (CBT), in adolescents with either depression, anxiety, or both, in combination with early-stage BPD.

**Methods:**

This study is a multi-centre randomized controlled trial. A total of 132 adolescents, presenting with either depression, anxiety, or both and significant BPD features will be randomized to either MBT-early or CBT. The severity of BPD, symptoms of depression and anxiety, personality, social and academic functioning, and quality of life will be assessed at baseline, end of treatment, and at 12-, 18-, and 24-month follow-up, along with medical costs and costs of productivity losses for cost-effectiveness analyses.

**Discussion:**

This study will provide an empirical evaluation of the potential surplus value of early intervention in young people for whom treatment oriented at common mental disorders like anxiety and depression may be insufficient given their underlying personality problems.

**Trial registration:**

Netherlands Trial Register, NL9569. Registered on June 15, 2021.

## Administrative information

Note: The numbers in curly brackets in this protocol refer to the SPIRIT checklist item numbers. The order of the items has been modified to group similar items (see http://www.equator-network.org/reporting-guidelines/spirit-2013-statement-defining-standard-protocol-items-for-clinical-trials/).

## Introduction

### Background and rationale {6a}

Borderline personality disorder (BPD) is a severe mental disorder associated with a range of unfavourable outcomes in several areas of mental, social, and occupational functioning [1–3]. Longitudinal data suggest that adult BPD typically is a chronic condition, characterized by patterns of remission and relapse at PD symptom level, but with more pervasive and persistent disabilities in psychosocial functioning [4, 5]. Community studies show that over half of the individuals with BPD are unemployed [6]. In addition, people with BPD often have poor physical health [3] and excess mortality from medical conditions [1] resulting in a high burden of disease and considerable societal costs [7, 8].

From an individual, societal, and (health-)economic perspective, it makes sense to switch from a focus on the late-stage treatment of BPD in adulthood to addressing emerging BPD in adolescence [9]. Symptoms of BPD typically emerge in adolescence [10], and evidence consistently suggests that negative outcomes, such as educational challenges, unemployment, and increased health care utilization and costs, are already prevalent during the transition from adolescence to young adulthood in persons with BPD [11, 12]. Accumulating data show that early intervention for BPD is time-sensitive, indicating adolescence as a critical juncture in the development of BPD, determining its course and long-term outcomes [13].

Despite this need for appropriate strategies for early intervention to reduce the short-term burden and prevent long-term disabilities, several studies suggest that current mental health services often do not provide an appropriate response to the health needs of these young persons. Data from the Netherlands [14] as well as Australia [15] show that young persons with BPD remain largely undetected in primary services, are not referred to appropriate treatment, and are rarely provided appropriate, evidence-based treatments. Brief psychosocial treatments that are common in primary care seem to be less effective for young people with BPD. For example, in a prospective follow-up study of young people receiving cognitive behavioural therapy (CBT) for depression, the subgroup of females with both depressive problems and BPD showed poor distal outcomes. These young people, compared to those without BPD, had up to four times higher likelihood of experiencing recurrent depressive episodes [16]. The limited effects of brief treatments for these young people seem to be in large part due to the considerable dropout rate from these treatments. Approximately 40–50% of young people with BPD drop out from treatment prematurely, even though they experience high levels of distress and suffering [17]. This suggests that these treatment approaches may not be adequately tailored to the specific needs and problems of young people with emerging BPD. In addition, current services are primarily organized based on a ‘stepped-care’ strategy; initiating care for these young people with brief and generic interventions which are subsequently upscaled in the case of poor response. Yet, poor or non-response in these young people is the rule rather than the exception. In a study on primary care in Australia for 12- to 25-year-olds, for instance, patients with BPD symptoms showed no progress or deteriorated in terms of social and occupational functioning (45%), psychological stress (60%), and quality of life (69%) [15]. Importantly, aside from the lack of efficiency in attaining, this approach generated iatrogenic damage in these youngsters as failed treatment attempts lead to disappointment in and distrust of mental health services [18], which may undermine future care-seeking or treatment success.

In response to the need for appropriate and in-time treatments, and the lack of evidence of treatment programmes for young people with BPD, the past decades have witnessed the development and evaluation of a range of treatment programmes for young people with BPD features, based on adaptations of treatments for BPD in adults. These include dialectical behaviour therapy (DBT-A) [19], mentalization-based treatment (MBT-A) [20], and transference-focused psychotherapy [21]. The evidence base for these adaptations is rather scarce. A recent review identified only ten randomized clinical trials [22–31]. The results indicate that the majority of these trials did not show the superiority of the specialized treatments compared with treatment as usual. Dropout rates varied widely, ranging from 15 to 75%. Moreover, the heterogeneity of the samples involved in these studies is typically large [17, 22]. Compared with treatments for adults with BPD, the majority of psychosocial treatments for young people with BPD were relatively brief (e.g. HYPE, consisting of sixteen sessions [23]) or were characterized by low treatment intensity (e.g. DBT-A, involving weekly sessions [26]). This matches a clinical staging perspective, with increasing consensus that such interventions, whether brief or low-intensity, may be best suited for addressing the early stages of BPD, characterized by low to moderate risk profiles [32]. However, these interventions are likely to be insufficient for young people with BPD at a later stage of development. A clinical staging approach may enable better matching of treatment to the clinical needs of these young people [10, 33]. Staged care has been introduced as an alternative to stepped care [34]. The advantages of such an approach are clear. Staged care does not require individuals to fail prior treatment to be assigned to more specialist services and it enables to match the type and level of care to the clinical needs associated with the stage of illness, also minimizing the probably of early dropout and dissatisfaction with and disbelief in mental health treatments.

### Objectives {7}

The primary aim of this study is to investigate the effectiveness of an early intervention approach for BPD (mentalization-based treatment-early [MBT-early]) compared to first-choice psychological treatment for depressive and anxiety disorders according to Dutch treatment guidelines (which is cognitive behavioural therapy [CBT]) for young people referred for treatment of depression, anxiety, or both, presenting with symptoms indicative of early-stage BPD. Treatment effects will be evaluated on the primary outcome (severity of borderline symptoms) and secondary outcomes (symptoms of depression and anxiety, personality functioning, social functioning, and academic functioning). Adolescents receiving MBT-early are expected to show superior outcomes in terms of severity of BPD symptoms and personality functioning, social functioning, and academic functioning compared to adolescents receiving CBT, but MBT-early will be non-inferior to CBT in reducing symptoms of depression and anxiety.

The secondary aim of this study is to compare the cost-effectiveness of both treatments based on costs per quality-adjusted life year (QALY). We expect MBT-early to be cost-effective compared to CBT.

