### Trial design {8}

This multi-centre study is a parallel-group, randomized controlled trial, where an early BPD intervention, MBT-early, is compared to first-choice psychological treatment, CBT, as recommended by the Dutch treatment guidelines, for adolescents with presenting symptoms of depression, anxiety, or both and emerging BPD symptoms. This study is a superiority trial comparing MBT-early and CBT at baseline, end of treatment, and at 12-, 18-, and 24-month follow-up. The allocation rate is 1:1.

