## Statistical methods

### Statistical methods for primary and secondary outcomes {20a}

Data analysis will be conducted using SPSS Statistics. Treatment outcomes of the primary outcome, severity of BPD symptoms, over time will be examined using multilevel modelling. Multilevel modelling is able to model data from different time points, correcting for the dependency of observations by adding a within-subject correlation structure to the regression model. Another advantage of multilevel modelling is that it is able to handle missing data, by using the available data irrespective of the number of repeated measurements. In other words, adolescents with an incomplete number of follow-up measurements are also included in the treatment outcome analyses.

The interventions will be compared with the intention-to-treat adolescent sample, that is, with all adolescents randomized to either MBT-early or CBT.

A deviance test using restricted maximum likelihood will be used to assess whether random or fixed slopes should be assumed in models for each outcome variable. Subsequently, time will be included as appropriate (i.e. linear, logarithmic) and included in the model together with the treatment group and time by group interactions if likelihood ratio tests show significant improvement. The primary effect size of the treatments will be estimated from baseline to end of treatment and secondary effect sizes from baseline to 12-, 18-, and 24-month follow-up. Additional treatment offered in the follow-up period will be included as a covariate in the estimation of the multilevel models and effect sizes from baseline to 12-, 18-, and 24-month follow-up, as well as a predictor of treatment outcomes at 12-, 18-, and 24-month follow-up.

The secondary outcomes will be analysed similarly using multilevel modelling, in which the type of model is adapted to the outcome if needed (i.e. binary in case of the C-SSRS) from baseline to end of treatment, 12-, 18-, and 24-month follow-up. As noted, additional treatment offered in the follow-up period will be included as a covariate in the estimation of the multilevel models and effect sizes from baseline to 12-, 18-, and 24-month follow-up, as well as a predictor of treatment outcomes at 12-, 18-, and 24-month follow-up.

To examine the possible influence of missing data, we will repeat the analyses described using datasets in which missing data are imputed with state-of-the-art data imputation methods [66].

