### Methods for additional analyses (e.g. subgroup analyses) {20b}

N/A. There are no additional analyses planned.

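### The protocol states a non-inferiority hypothesis for depression and anxiety, but its design and analysis sections give that hypothesis no valid test

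*Protocol article*

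**What the plan says.** The Objectives section of the protocol article separates two kinds of expectation in one sentence. Superiority of MBT-early is expected on BPD severity and on personality, social and academic functioning. For the presenting symptoms the claim is different: "MBT-early will be non-inferior to CBT in reducing symptoms of depression and anxiety".

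The Trial design section frames the whole study one way: "This study is a superiority trial comparing MBT-early and CBT at baseline, end of treatment, and at 12-, 18-, and 24-month follow-up". The Sample size section is based on the BPDSI-IV-ado alone: d = 0.50, two-sided α = 0.05, power 0.80, a correlation of 0.50 between repeated measures, 59 per group, and 66 per group after 10% attrition.

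The Statistical methods section states: "The secondary outcomes will be analysed similarly using multilevel modelling, in which the type of model is adapted to the outcome if needed". In the model it refers back to, time enters together with treatment group and "time by group interactions if likelihood ratio tests show significant improvement". The comparison is by intention to treat ("The interventions will be compared with the intention-to-treat adolescent sample"), and the section on additional analyses says "There are no additional analyses planned". The same Statistical methods section also undertakes to estimate effect sizes, from baseline to end of treatment as the primary interval and to the later visits as secondary ones.

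**The concern.** A non-inferiority conclusion needs an estimated difference, its confidence interval, and a limit fixed in advance against which the interval is judged. The analysis described is organised around whether a group term significantly improves the model. A significant result would show a difference. A non-significant one would show neither equality nor non-inferiority, and if the term then leaves the model there may be no interval left to judge.

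This matters because participants are referred for depression or anxiety and CBT is the guideline first choice for both. Whether MBT-early loses ground on those symptoms is something readers will want answered. The stated hypothesis invites them to look for an answer that the described analysis does not supply.

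**Working it through.** **Side by side.** Objectives: non-inferiority on depression and anxiety. Trial design: superiority. Sample size: superiority on a different outcome. Statistical methods: the same model-building by significance, with no rule for non-inferiority. None of the last three supports the first.

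**The plan's own figure.** The usual two-group formula, n = 2V[(1.96 + 0.842)/0.50]², gives 63 per group for V = 1 (a single post-treatment score, or a change score at r = 0.5, since 2(1 − 0.5) = 1). It gives 48 for V = 1 − 0.5² = 0.75 (baseline-adjusted). The stated 59 lies between the two and is not reproduced, but the protocol gives no formula and nothing below depends on resolving this. The attrition step does reproduce: 59/0.90 = 65.6, so 66. I take 59 per arm as given.

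**Inputs for the check.** n = 59 per arm and r = 0.5, both from the Sample size section. They were set for the BPDSI-IV-ado, so applying them to PHQ-9 and GAD-7 is an assumption. Differences are in SD units. The protocol gives no margin, so the margins used are illustrative.

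**Precision.** SE = √(2V/59).
- V = 1: SE = 0.184 SD and 95% CI half-width 1.96 × 0.184 = 0.36 SD.
- V = 0.75: SE = 0.159 SD and half-width 0.31 SD.

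An observed difference against MBT-early that just fails to reach significance would have an interval reaching twice the half-width: about 0.72 SD worse (0.63 SD adjusted).

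**Chance of a non-significant result when MBT-early is truly worse by δ.** P = Φ(1.96 − δ/SE) − Φ(−1.96 − δ/SE). For δ = 0.3 and V = 1, δ/SE = 1.629, so P = Φ(0.331) − Φ(−3.589) = 0.629.

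| True disadvantage | Unadjusted | Baseline-adjusted |
|---|---|---|
| 0.3 SD | 63% | 53% |
| 0.4 SD | 42% | 29% |
| 0.5 SD | 22% | 12% |

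**Power of a proper non-inferiority test with equal true effects.** Power = Φ(margin/SE − 1.96). Number needed per group for 80% power, before attrition: n = 2V[(1.96 + 0.842)/margin]².

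| Illustrative margin | Power at 59 per arm, unadjusted / adjusted | Needed per group, unadjusted / adjusted |
|---|---|---|
| 0.3 SD | 37% / 47% | 175 / 131 |
| 0.4 SD | 58% / 71% | 99 / 74 |
| 0.5 SD | 78% / 88% | 63 / 48 |

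These figures are for one outcome. Requiring both PHQ-9 and GAD-7 to succeed would lower the power.

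**The case against.** The strongest reply is that this is a condensed article. A margin, a confidence-bound rule and a choice of instrument for a secondary hypothesis commonly sit in the full protocol or SAP, which are not shown. That stands: a missing margin alone would be no finding. What remains is that the article itself states one hypothesis and then describes a framework and an analysis that do not match it. An SAP that followed the article would repeat the mismatch.

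A superiority label may also refer to the primary outcome, and such a trial can carry a non-inferiority hypothesis on a secondary domain. That is fair, and the protocol does not say superiority is the only framework. But the secondary domain then needs its own decision rule, and the analysis text sends it back to the primary outcome's method.

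Three stronger readings are tempting and are not supported:

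- A reader might infer that non-significance will be read as non-inferiority. No section says so; it is a risk left open by the lack of any other rule.
- A reader might infer that the model is incapable of a non-inferiority test. It is not. A multilevel model yields a difference and an interval, and the protocol commits to estimating effect sizes. The likelihood ratio clause makes it uncertain whether the interaction estimate is always retained, and no rule says how to judge it.
- A reader might count five instruments in this domain as five open carriers of the claim. The Secondary outcomes section includes BSI and CBCL for comparison with other MBT trials and C-SSRS for suicidality, which leaves PHQ-9 and GAD-7 as the natural pair.

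It is also true that the trial was not sized for this domain. Limited power there is not in itself a design error.

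**Conclusion.** The point holds as an internal mismatch. The non-inferiority hypothesis on depression and anxiety has no valid test in the plan as described. Its practical weight is the risk of false reassurance: a true 0.3 SD disadvantage would go undetected in roughly 53% to 63% of trials of this size. That figure rests on 59 analysed per arm, r = 0.5 carried over from the BPDSI-IV-ado, and a normal approximation to the end-of-treatment contrast. The choice of 0.3 SD is illustrative.

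The outcomes concerned are secondary. The primary BPDSI-IV-ado comparison and the cost-effectiveness aim are untouched, so this is something the team should fix, not a defect that undermines the trial.

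**What to change.** For PHQ-9 and GAD-7, keep the group-by-time term in the model whatever its p-value, and report the end-of-treatment difference with its 95% CI. Then choose one of two routes:

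1. Fix a clinically justified margin, in scale points, before any unblinded data are seen. Conclude non-inferiority only if the whole interval lies on the acceptable side of it. A per-protocol analysis may be added as support, because non-completion and later receipt of the other treatment, which the protocol allows, tend to make the arms look alike.
2. Reword the hypothesis as descriptive, and state that a non-significant difference will not be read as non-inferiority.

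The Objectives and Trial design sections should then be brought into line with the route chosen. The cost is a small amendment and one paragraph in the analysis plan, with no new data collection. The downside of the first route is that, with about 59 per arm, the trial may be unable to show non-inferiority for margins much tighter than about 0.4 to 0.5 SD. The second route avoids this by giving up the claim.

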### Trial design {8}

This multi-centre study is a parallel-group, randomized controlled trial, where an early BPD intervention, MBT-early, is compared to first-choice psychological treatment, CBT, as recommended by the Dutch treatment guidelines, for adolescents with presenting symptoms of depression, anxiety, or both and emerging BPD symptoms. This study is a superiority trial comparing MBT-early and CBT at baseline, end of treatment, and at 12-, 18-, and 24-month follow-up. The allocation rate is 1:1.

## Methods: participants, interventions, and outcomes

### Study setting {9}

Three mental healthcare institutions in the Netherlands participate in this study: Mentaal Beter (Bergen op Zoom, Roosendaal, Etten-Leur, and Breda), GGz Breburg (Breda), and de Viersprong (Bergen op Zoom). All three of these institutions provide treatments for young people referred for (emerging) mental health problems and offer interventions for a wide range of mental health problems. GGz Breburg provides both MBT-early and CBT, while Mentaal Beter only provides CBT and de Viersprong solely provides MBT-early. Consequently, adolescents referred to Mentaal Beter and randomized to MBT-early will receive treatment administrated by therapists from de Viersprong, while those referred to de Viersprong and randomized to CBT will be treated at Mentaal Beter.

### Eligibility criteria {10}

Adolescents are eligible for this study if they meet the following criteria: (a) adolescents between 12 and 18 years old; (b) a depression, anxiety disorder, or both as assessed by the Structural Clinical Interview for DSM-5 Syndrome Disorders (SCID-5-S; [35]); and (c) early stage BPD, defined as three to six features of BPD and mild and moderate disabilities in either school, with family, or with peers or in multiple areas as assessed using the structural clinical interview for DSM-5 Personality Disorders (SCID-5-P; [36]). The exclusion criteria are (a) a primary diagnosis that requires other specialist treatment (e.g. severe autism spectrum disorder, chronic psychotic disorder, severe eating disorder, or severe substance abuse disorder), (b) IQ < 75, or (c) severe disability with regard to functioning in school, at home, and in the peer group representative for later stage BPD [10].

### Who will take informed consent? {26a}

All consecutively referred adolescents between 12 and 18 years old referred to the above mental health care institutions for treatment of presenting symptoms of depression, anxiety, or both, and their parents, will be informed about the study during the first consultation with a mental health professional. They will receive an information letter with detailed information about the study and the screening process. If the adolescent agrees to participate in the screening process, the mental health professional obtains informed consent for the screening process from the adolescent, and from both parents if aged under 16, and asks permission to share their contact information with the research team. The adolescent and parents have at least 1 week to consider their decision about participating in the screening process. After approval for the screening, a research assistant contacts the family to plan the screening. If the inclusion criteria are met, the mental health professional will inform the family that the adolescent is eligible to participate in the study during the second consultation. Again, the adolescent and parents have at least 1 week to consider their decision about participating in the study. If they agree, the research assistant will obtain informed consent for participating in the study from the adolescent, and from both parents if aged under 16, and plan the baseline assessment. After baseline assessment, the adolescent will be randomly assigned to MBT-early or CBT (for more details, see the ‘Assignment of interventions: allocation’ section).

